## Hyperalgesia testing

The hyperalgesia testing is the same as described in the protocol for our related trial [IMI2-PainCare-BioPain-RCT3] see [2] for more details. Briefly, the intensity of the sensation elicited by calibrated mechanical pinprick stimuli will be assessed at the left (HFS-sensitized) and right (non-sensitized) sides. At the sensitized sites, the extent of the area of secondary hyperalgesia will be measured by locating the position at which subjects report a change in the intensity of the sensation elicited by mechanical pinprick stimuli delivered along 8 radial directions. The same approach will be used to assess the intensity and area of dynamic allodynia (if present), using a standardized Q-tip to deliver tactile stimuli.

### Plans to promote participant retention and complete follow-up {18b}

The plans to promote participant retention and complete follow-up are not the same as descibed in the protocol for our related trial [IMI2-PainCare-BioPain-RCT3] see [2] for more details.

### Data management {19}

The data management is the same as described in the protocol for our related trial [IMI2-PainCare-BioPain-RCT3] see [2] for more details. Briefly, data management will be performed by the Heidelberg University Computing Centre. Documentation of the responsibilities and delegation thereof will be maintained in the trial master file.

All aspects of the data management process have been specified in RCT3 [2] and are detailed in the Data Management Plan.

All source data arising from the trial will be kept by the investigator, who will provide direct access for trial-related monitoring, audits, ethics committee review, and regulatory inspection.

Case report forms for each subject will be provided to the investigator in electronic format and will serve to create the local source documentation in paper format. The investigator and delegated personnel will use these paper-form documents to record the source data information required by the protocol. The source data documentation will be entered into a validated electronic CRF system via a secured access to the Research Electronic Data Capture (REDCap) database hosted at the Heidelberg University computing center. The collected data will reside on secure servers of the Heidelberg University. Entry, corrections, and alterations of data within the system can only be performed by the investigator or other authorized personnel under their supervision and will be captured by the system’s audit trail. Users will be trained and receive access rights according to their role in the trial. All users will have access to the system and be able to review their data on an ongoing basis. After completion of the subject’s CRF, the CRF will be signed electronically by the investigator to confirm that the data are checked, complete, accurate, and in alignment with the source data. With database lock, the edit rights to the CRFs will be removed, but the investigator will retain access to view the CRFs. The nature and location of all source data/clinical documentation will be identified and documented by the investigator to ensure that all sources of original data required to complete the CRF are known to the sponsor and/or trial site personnel and are accessible for verification during trial-related monitoring, audits, relevant IEC review, and inspection(s). During trial conduct, the Heidelberg University Computing Centre is responsible for data security related to the data captured in the CRF.

Pharmacodynamic data will also be transferred to the Heidelberg database and data will be extracted centrally at Sapienza University where the data will be stored on secured servers. Derived data will be transferred to the relational database hosted at the Heidelberg University computing center. Pharmacokinetic concentrations and pharmacokinetic parameters measured by Welab will be uploaded by Welab to the relational database at the Heidelberg University computing center. Investigator site file and trial master files will be kept according to GCP.

### Confidentiality {27}

Subject trial data will be stored in a manner maintaining confidentiality in accordance with applicable regulatory requirements.

The source data will be pseudoanonymized and encoded (i.e., name and social security number), so to avoid the possibility to identify the individual persons.

### Plans for collection, laboratory evaluation, and storage of biological specimens for genetic or molecular analysis in this trial/future use {33}

This is described in detail for RCT3 [2] and is summarized here.

The analysis of drug levels at all the different sampling times will be performed on pharmacokinetic samples collected from trial subjects who will be randomized to receive an active treatment (tapentadol, pregabalin, or lacosamide). Placebo samples will be analyzed at a single time point around *t*_max_ of drugs.

Drug concentrations of tapentadol, pregabalin, and lacosamide will be analyzed by Welab Bioanalysis and ADME Development Department using a validated method under GLP (Good Laboratory Practice). The three drugs will be identified and quantified using HPLC method with tandem mass spectrometric detection (LC-MS/MS). Full details of the different analytical methods used will be described in the respective bioanalytical method validation report, and drug levels quantified in human plasma samples will be also reported in the respective bioanalytical report.

The bioanalytical laboratory will be unblinded in order to analyze multiple time points from the specific active treatments and single time points from corresponding placebos. The analysis will be conducted when the clinical study is finished but the dataset is not yet locked ensuring that sponsor remain blinded by recoding the subject’s numbers.

For each compound, relevant PK parameters will be calculated by standard non-compartmental methods for those subjects with sufficient plasma concentration data using Phoenix 64® WinNonLin® (Version 6.3 or later) with a log-linear terminal phase assumption. All reported sampling time deviations will be taken into consideration for evaluation of PK parameters.

For all three drugs, the following standard non-compartmental pharmacokinetic parameters and drug-exposure-related metrics will be estimated in each subject, including:*C*_max_: maximum plasma concentration.*t*_max_: time to reach maximum plasma concentration.λz: the terminal phase constant will be calculated by linear regression of the last phase of the curve (log concentration vs time).*t*_1/2_: terminal half-life will be determined with the expression *t*_1/2_= 0.693/λz.AUC0-t: Area under the plasma concentration-time curve from time zero to last quantifiable concentration calculated by the linear and/or log trapezoidal rule.AUC0-∞: The area under the curve of plasma levels vs time from zero to infinite will be obtained with the expression AUC0-∞= AUC0-t +Clast/λz, where Clast is the predicted plasma concentration at the last time measured.

A descriptive analysis will be provided for each derived PK parameter. Below limit of quantitation (BLQ) concentrations will be treated as zero for all statistical analyses.

Full details of the pharmacokinetic analysis and the corresponding statistical analysis of PK parameters will be described in the final report.

## Statistical methods

### Statistical methods for primary and secondary outcomes {20a}

This and the following sections briefly specify the statistical analysis principles for the study. Final and detailed specifications on the quantitative analyses described here will be provided correspondingly in the statistical analysis plan to be finalized prior to unblinding of the study. The statistical procedure for the selected, confirmatory analyses will follow the sequentially rejective multiple testing approach described by Bretz et al. [33]. The two primary endpoints, change in the RIII area at the sensitized limb and in the N13-SEP amplitude after stimulation of the sensitized hand, will be tested for their differences between the treatment arm tapentadol versus placebo, first. This will be conducted in parallel, splitting the overall *α* equally between the endpoints’ tests, i.e., each test has a type I error of *α*/2. If any of these two tests shows significant differences, key secondary analyses will be conducted using the *α*-levels as passed on from initial/prior tests according to specified weights. The exact procedure (with the local levels as well as the weights with which to pass *α*-levels on) is illustrated by in Fig. 3.

**Fig. 3 Fig3:**
[figure not shown]
Statistical procedure

#### Definition of the primary endpoints

RIII flexion reflex change endpoint data being repeated measurements across the four periods will be analyzed with a mixed effect model with treatment (4 levels), period (4 levels), and center and sequence as fixed effects. The variance-covariance structure for the repeated measure variable period should be chosen as UN (unstructured), TOEPH (heterogeneous Toeplitz), CSH (heterogeneous compound symmetry), ARH(1) (heterogeneous AR(1)), TOEP (Toeplitz), CS (compound symmetry), and AR(1) (first order autoregressive) in that order of preference.

The least squares (LS) mean difference of treatment active treatment versus placebo will be estimated based on this model and the estimate as well as the corresponding unadjusted confidence interval and *p*-value will be provided.

The analysis for the N13-SEP change is similar and details will be provided in the analysis plan.

If either (or both) of the primary endpoints’ tests show significant differences between tapentadol and placebo, in the sense that the *p*-value is below the corresponding local alpha level, the differences are confirmed and the testing procedure continues according to the graph above.

### Definition of secondary endpoints

These statistical analyses are considered confirmatory only provided they have received local *α*-levels (type I error greater than 0) from prior tests rejecting their corresponding null hypotheses. The method for testing the secondary endpoints comparing the other treatment groups versus placebo mirrors the model specifications of the primary analysis above but using the Dunnett-adjusted estimation and testing results to compare pregabalin and lacosamide with placebo respectively. The method for testing the key secondary endpoint for R2 recovery cycle is identical to the specifications of the primary analysis above.

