**Key secondary analyses of the primary endpoints:**	
1. To test if the percentage of change of the RIII area of the flexion reflex at the time point t60 post-drug administration vs the pre-drug time point, differs in the pregabalin and/or lacosamide period as compared to the placebo period, at the sensitized lower limb.	
2. To test if the percentage of change of the N13-SEP amplitude at the time point t60 post-drug administration vs the pre-drug time point, differs in the pregabalin and/or lacosamide period as compared to the placebo period, at the sensitized upper arm.	
3. To test if the percentage of change of the R2 recovery cycle at 500 ms interstimulus time interval at the time point T60 post-drug administration vs the pre-drug administration differs in the tapentadol, pregabalin and/or lacosamide periods as compared to the placebo period.	

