According to the sequentially rejective multiple testing design, two primary endpoints will be tested simultaneously at alpha/2; these are pairwise comparisons of one medication vs. placebo for one post-medication time point and one readout variable that are most likely to be significant, based on published literature (see power calculation). Three key secondary endpoints are assessed, given that alpha levels were passed successfully from one or both of the primary endpoints or from one or both of the other key secondary endpoints. All efficacy analyses will be done on data pooled across participating centers; efficiency of this multicenter study approach in human volunteers will be assessed by comparing across-center vs. within-center variability of the various readout variables.

In addition to the analysis of the individual RCTs, biomarker results and pharmacokinetic and pharmacodynamics analyses will be compared across trials and to preclinical studies and will possibly try to establish a latent variable model of underlying mechanisms at peripheral, spinal, and brain levels. Pain ratings will be included as another readout variable, and questionnaires on psychological traits predictors (e.g., catastrophizing, anxiety) will also be analyzed as potential predictors of pain and analgesia. By identifying specific mechanisms within different compartments of the nociceptive system in healthy volunteers, these same quantitative neurophysiological biomarkers, if well validated against clinically meaningful outcomes in patients, may be used for patient stratification and enrichment in later clinical trials, as encouraged by the recent EMA/CHMP/970057/2011 Guideline. This will accelerate the development of novel analgesics in several ways: preclinical prediction will be improved by using translatable readouts across species; clinical Phase 1 trials will benefit from biomarkers of target engagement and from human surrogate models predictive of clinical efficacy; clinical Phase 2 and 3 studies will benefit from tools for patient stratification.

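### Optional efficiency gain: step-down Dunnett for pregabalin and lacosamide would raise the chance of confirming both drugs at the same local alpha; the Dunnett test as planned is valid

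*Protocol article*

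**What the plan says.** Under Definition of secondary endpoints, the comparisons of pregabalin and lacosamide with placebo reuse the primary model, "using the Dunnett-adjusted estimation and testing results to compare pregabalin and lacosamide with placebo respectively". Neither single-step nor step-down is named. The model is a "mixed effect model with treatment (4 levels), period (4 levels), and center and sequence as fixed effects" (Definition of the primary endpoints).

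Table 4 words the key secondary question on RIII as whether the change "differs in the pregabalin and/or lacosamide period as compared to the placebo period, at the sensitized lower limb"; the N13 question has the same form.

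Section {20a} says that the confirmatory strategy "will follow the sequentially rejective multiple testing approach". For the two tapentadol tests, "each test has a type I error of *α*/2". After a success, "key secondary analyses will be conducted using the *α*-levels as passed on from initial/prior tests according to specified weights". The Discussion adds that a key secondary endpoint may receive alpha "from one or both of the primary endpoints or from one or both of the other key secondary endpoints". The local levels and weights are in Fig. 3, which is not shown. Section {20a} leaves detailed specifications to an SAP, which is not available here.

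**The concern.** Adjusted estimates paired with adjusted tests are the ordinary output of single-step Dunnett. Under that procedure the second drug must still clear the two-comparison threshold after the first has been rejected. By the closure principle this is unnecessary: once the first null hypothesis is rejected, the only one left in the pair is a single drug-placebo comparison, which can be tested at the full local alpha. Single-step Dunnett therefore leaves part of the permitted error unused.

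What is at stake is power to confirm both drugs on RIII or on N13. The protocol sets out to profile three compounds with different preferred sites of action, and each drug is compared with placebo separately, so a result on both is of interest.

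**Working it through.** **Plan's own figures.** No power is stated for these comparisons. Sample size {14} gives power only for a paired t-test on RIII: about 90% at 32 subjects, and about 70 to 75% at 40 or 44. If the quoted SDs are taken as SDs of paired differences, I get 0.973 to 0.993 at 32 and 0.857 to 0.939 at 40 or 44 (two-sided alpha 0.025 to 0.05). With the SD of the difference set to √2 × SD (normal approximation, alpha 0.05), I get 0.897 at 32 (0.866 from the percentage figures) and 0.676 and 0.717 at 40 and 44. The stated figures are thus not reproduced without a further assumption. That does not affect this point: 70 to 75% and 90% serve below only as reference levels.

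**Assumed inputs, not in the protocol.** Overall alpha is 0.05 two-sided. Local alpha at this step is 0.0125 to 0.05. The two drug-placebo contrasts correlate 0.5 through the shared placebo. Degrees of freedom are 120 to 160; for 44 completers, 44 × 3 − 3 (period) − 3 (treatment) = 126.

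**Decision rules.** Let c2 be the two-sided Dunnett value for two comparisons and c1 the unadjusted value.
- Single-step confirms both drugs if both |t| > c2.
- Step-down confirms both if the larger |t| > c2 and the smaller |t| > c1.
- Either method confirms at least one drug if the larger |t| > c2, so that probability is identical (for example 0.769 at 70% power per drug and local alpha 0.025).

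Critical values (c2 / c1) are 2.24 / 1.98 at local alpha 0.05, 2.51 / 2.27 at 0.025 and 2.77 / 2.53 at 0.0125.

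**Probability of confirming both drugs, single-step → step-down.** Equal effects, 120 df. Rows are each drug's unadjusted power at its local alpha. Gains in points are from unrounded values.

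| Power per drug | alpha 0.05 | alpha 0.025 | alpha 0.0125 |
|---|---|---|---|
| 30% | 0.100→0.149 (+4.9) | 0.103→0.150 (+4.7) | 0.106→0.151 (+4.5) |
| 50% | 0.240→0.323 (+8.3) | 0.246→0.325 (+7.9) | 0.251→0.326 (+7.6) |
| 70% | 0.447→0.548 (+10.0) | 0.454→0.549 (+9.5) | 0.460→0.551 (+9.1) |
| 75% | 0.513→0.612 (+10.0) | 0.520→0.614 (+9.4) | 0.525→0.615 (+9.0) |
| 90% | 0.755→0.828 (+7.3) | 0.761→0.829 (+6.9) | 0.765→0.830 (+6.5) |
| 95% | 0.860→0.910 (+5.0) | 0.864→0.910 (+4.6) | 0.867→0.911 (+4.4) |
| 99% | 0.965→0.981 (+1.6) | 0.966→0.981 (+1.5) | 0.967→0.981 (+1.4) |

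With equal effects the gain per drug is half of this, because each extra double confirmation adds one rejection shared between two drugs (9.5 / 2 = 4.75 points at 70% and alpha 0.025).

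**Sensitivity.** Powers of 90% and 30% for the two drugs give +7.3 to +8.1 points; 75% and 10% give +3.2 to +3.6. At 75% power each, contrast correlations of 0.3 to 0.7 give +7.5 to +11.3.

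**Error within the pair.** With one drug strongly effective and the other null, step-down rejects the null drug at exactly the local alpha (0.050 or 0.025). Single-step rejects it at 0.027 or 0.013. Both stay within the limit.

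**Error beyond the pair.** Suppose a single rejection released the full local alpha of 0.05 to a further, independent null endpoint, with one drug strongly effective and the other null. The error would be 1 − (1 − 0.027)(1 − 0.05) ≈ 0.076 under single-step and 1 − 0.95² ≈ 0.098 under step-down. If alpha leaves only after both rejections, the null drug must be falsely rejected before any alpha moves on, so the error stays at 0.027 and 0.050.

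**The case against.** The strongest reply is that nothing here is wrong. Dunnett-adjusted tests against a shared placebo are standard and control error, and the single-step form gives intervals that agree with its tests. That stands.

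Single-step is also an inference: the article names no variant and leaves details to the SAP. That stands too, though pairing adjusted estimation with adjusted testing makes single-step the natural reading.

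The gain depends on effects that the protocol does not supply. It gives none for pregabalin or lacosamide, and it says that no reliable figures exist for N13. Because Objectives {7} assigns lacosamide a mainly peripheral and pregabalin a mainly spinal action, equal effects on spinal readouts cannot be presumed. For the one-or-both wording in Table 4 the gain is nil if success means at least one drug. The tests are confirmatory only if alpha reaches them. All of this narrows the claim. It does not remove it, because step-down is never less powerful.

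A reader might infer that single-step Dunnett contradicts the sequentially rejective strategy in {20a}. It does not: that wording describes how alpha moves between tests, and a valid local-level test may sit inside one step.

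**Conclusion.** A worthwhile, inexpensive improvement, not a defect. Read as single-step, the planned test is valid but leaves power to confirm both drugs unused. The gain is about 7 to 10 points when each drug has roughly 50 to 90% power, and about 1 to 5 points at lower or higher power or with very unequal effects. It is zero for confirming at least one drug.

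These sizes rest on an overall two-sided alpha of 0.05, local levels of 0.0125 to 0.05, a contrast correlation of 0.5 and 120 or more degrees of freedom. Two stronger readings are not supported. An unconditional gain of 7 to 10 points would need effect sizes that the protocol does not give. Unchanged error control across the whole testing graph is shown only within the pair; beyond it, control depends on how Fig. 3 releases alpha.

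**What to change.** In Definition of secondary endpoints and in the SAP, before unblinding, specify step-down Dunnett at the step's local alpha. Test the drug with the larger |t| at the two-comparison Dunnett value (2.51 at 0.025, about 126 df assumed). If it is rejected, test the other drug at the unadjusted value (2.27). State that alpha is passed on from this step only after both drugs are rejected, and check that against Fig. 3. If the SAP already specifies step-down, one clarifying sentence in the protocol is enough.

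Keep the single-step simultaneous intervals for estimation. The cost is about one sentence and one line of code, plus a footnote that such an interval may include zero for a drug rejected only at the second step.

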**Methods:**

This is a multisite, single-dose, double-blind, randomized, placebo-controlled, 4-period, 4-way crossover, pharmacodynamic (PD) and pharmacokinetic (PK) study in healthy subjects. Neurophysiological biomarkers of spinal and brainstem activity (the RIII flexion reflex, the N13 component of somatosensory evoked potentials (SEP) and the R2 component of the blink reflex) will be recorded before and at three distinct time points after administration of three medications known to act on the nociceptive system (lacosamide, pregabalin, tapentadol), and placebo, given as a single oral dose in separate study periods. Medication effects on neurophysiological measures will be assessed in a clinically relevant hyperalgesic condition (high-frequency electrical stimulation of the skin), and in a non-sensitized normal condition. Patient-reported outcome measures (pain ratings and predictive psychological traits) will also be collected; and blood samples will be taken for pharmacokinetic modelling. A sequentially rejective multiple testing approach will be used with overall alpha error of the primary analysis split between the two primary endpoints, namely the percentage amplitude changes of the RIII area and N13 amplitude under tapentadol. Remaining treatment arm effects on RIII, N13 and R2 recovery cycle are key secondary confirmatory analyses. Complex statistical analyses and PK-PD modelling are exploratory.

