#### Primary and key secondary outcomes

The two primary and the three key secondary endpoints (Table 4) are the treatment-induced percentage change of the RIII flexion reflex area and the N13-SEP amplitude elicited by stimulation of the sensitized limb and the treatment-induced percentage change of R2 recovery cycle at different interstimulus time intervals after supraorbital nerve stimulation of the non-sensitized side.

**Table 4 Tab4:** Primary and key secondary endpoints

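### The R2 key secondary compares three drugs with placebo but is assigned the primary analysis's unadjusted test, so unless Fig. 3 separates the contrasts it runs at about 2.5 to 2.7 times its local level

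*Protocol article*

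**What the plan says.** All references are to the protocol article.

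- **Framework.** The abstract's Methods describe a sequentially rejective procedure with the "overall alpha error of the primary analysis split between the two primary endpoints", and list the remaining treatment effects on RIII, N13 and R2 as confirmatory key secondaries. Section {20a} says of the two primary comparisons that "each test has a type I error of" alpha/2, and refers to Fig. 3 for the local levels and the weights.
- **Primary method.** Under *Definition of the primary endpoints*, the mixed model gives a difference between active drug and placebo. What is reported is "the estimate as well as the corresponding unadjusted confidence interval" and the p-value, which is compared with the local alpha. Each primary endpoint has one contrast, tapentadol against placebo.
- **R2 hypothesis.** Table 4, key secondary item 3, asks whether R2 recovery at 500 ms "differs in the tapentadol, pregabalin and/or lacosamide periods as compared to the placebo period". That is three contrasts.
- **R2 method.** *Definition of secondary endpoints* uses Dunnett for pregabalin and lacosamide against placebo. The next sentence reads: "The method for testing the key secondary endpoint for R2 recovery cycle is identical to the specifications of the primary analysis above".
- **How R2 is counted.** *Primary and key secondary outcomes* and the Discussion both count three key secondary endpoints, with R2 as one of them. The Discussion says: "Three key secondary endpoints are assessed, given that alpha levels were passed successfully from one or both of the primary endpoints". It adds that alpha may also come from the other key secondaries.

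**The concern.** Two adjacent sentences treat the same problem differently. Two drugs against a common placebo get a multiplicity adjustment; three drugs against the same placebo get none. An unadjusted p-value is right for the primary analysis because each primary endpoint has a single contrast. Carried over to R2, the same rule gives three chances of a positive finding at one local level.

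What is at stake is the confirmatory label on R2. The graph protects the family-wise error only if each element is tested at the level it was given. If R2 spends more than its local level, strong control is no longer assured in the situations where R2 is actually tested, that is, after alpha has been passed to it.

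**Working it through.** **Inputs**

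- Overall alpha: given only as a symbol. I assume 0.05 two-sided.
- Initial split: alpha/2 for each primary test ({20a} and Discussion).
- R2 contrasts: 3 (Table 4, item 3).
- R2 local level *a*: not known without Fig. 3. I show 0.05, 0.025 and 0.0125.
- Correlation between R2 contrasts: assumed 0.5. With equal variances and a balanced crossover, each drug-minus-placebo difference has variance proportional to 2 and any two share a covariance proportional to 1, so the correlation is 1/2. I also show independence and the Bonferroni bound.

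**Step 1. The plan's own figure.** The split reproduces: alpha/2 + alpha/2 = 0.025 + 0.025 = 0.05. Nothing is wrong with the primary tests.

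**Step 2. Three unadjusted contrasts at one local level.** Let c be the two-sided normal critical value for level *a*, and let all three R2 null hypotheses be true. With rho = 0.5,

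P(at least one rejection) = 1 − ∫ φ(x) · [Φ((c − √rho·x)/√(1 − rho)) − Φ((−c − √rho·x)/√(1 − rho))]³ dx.

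Under independence it is 1 − (1 − a)³, and the Bonferroni bound is 3a.

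| Local level a | rho = 0.5 | Ratio to a | Independent | Upper bound |
|---|---|---|---|---|
| 0.05 | 0.1254 | 2.5 | 0.1426 | 0.15 |
| 0.025 | 0.0655 | 2.6 | 0.0731 | 0.075 |
| 0.0125 | 0.0338 | 2.7 | 0.0370 | 0.0375 |

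A simulation with t statistics for 40, 44 and 56 subjects (error degrees of freedom 3(n − 1) − 3 = 114, 126 and 162) gave 0.124 to 0.125 at level 0.05 and 0.064 to 0.065 at level 0.025. The normal figures are therefore adequate at this sample size.

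**Step 3. When R2 alone passes 5%.** Setting the integral equal to 0.05 and solving for the local level gives a = 0.0188. Above that level, R2 by itself exceeds an overall alpha of 0.05. Below it, R2 still exceeds its own share, but whether the whole procedure exceeds 0.05 depends on the weights.

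**Step 4. Global null.** If every null hypothesis is true, R2 is reached only after a false primary rejection. The family-wise error is then at most 0.025 + 0.025 = 0.05, whatever is done at R2. The problem arises only when at least one primary null is false and alpha reaches R2.

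**Step 5. With Dunnett over three contrasts.** Solving the same integral for the critical value that returns the local level:

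| Local level | Critical \|z\| | Per-contrast p below |
|---|---|---|
| 0.05 | 2.349 | 0.0188 |
| 0.025 | 2.607 | 0.0091 |
| 0.0125 | 2.843 | 0.0045 |

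**The case against.** The strongest reply is that Fig. 3 is not available to this review. In a sequentially rejective graph it is standard to compare an unadjusted p-value with a hypothesis's own local level. If Fig. 3 gives each R2 contrast its own node, the sentence sending R2 to the primary method is correct and needs only clarifying. This stands as a real limit. The text leans the other way, though: R2 is counted as one of three key secondaries, and Dunnett for pregabalin and lacosamide within RIII and N13 makes sense if the drugs share a level and would be redundant if each had its own.

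Two other readings help less. If the R2 sentence meant tapentadol only, it would contradict Table 4, which lists three drugs. If a claim on R2 required all three contrasts to be significant, no adjustment would be needed, but the and/or in Table 4 does not require that. Nor is the point simply left to the analysis plan: the article names a method for R2.

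The trial also calls itself exploratory under *Trial design*, and R2 is tested only conditionally. This bears on severity, but the same article labels these analyses confirmatory.

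A reader might be tempted to go further in two ways, and the documents support neither.

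- **Alpha released too early.** One might infer from the and/or that a key secondary passes its alpha on after only one drug is positive. No section states such a release rule. Table 4 describes hypotheses, not transfers, so an overall error figure built on that rule would rest on an assumed graph.
- **More R2 contrasts.** The endpoint summary speaks of the "treatment-induced percentage change of R2 recovery cycle at different interstimulus time intervals", which could suggest further contrasts. Table 4 fixes 500 ms for the key secondary, and 250 and 750 ms are listed as exploratory.

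**Conclusion.** The point holds conditionally and should be fixed; confidence is moderate. As the text stands, R2 has three contrasts and an unadjusted test. Unless Fig. 3 separates those contrasts, the R2 test runs at about 2.5 to 2.7 times its local level under correlation 0.5, and at no more than 3 times under any correlation.

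It would go too far to say that the trial's family-wise control fails outright. That needs the R2 contrasts to share one level, which is inferred, and alpha to have reached R2. The size of any overall excess depends on weights not available here and on an overall alpha that the article never gives as a number. The ratio itself depends little on that assumed alpha.

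**What to change.** Under *Definition of secondary endpoints*, replace the R2 sentence with wording such as: *R2 at the 500 ms interval: same model as the primary analysis, with tapentadol, pregabalin and lacosamide each compared with placebo using Dunnett adjustment for three comparisons at the local alpha of the R2 node.* If Fig. 3 already gives each R2 contrast its own node and level, say that there instead, and no adjustment is needed. Make the same statement in the analysis plan before unblinding.

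The cost is wording only, with no change to data collection. R2 critical values become somewhat stricter: at a local level of 0.025, for example, each contrast would need p below about 0.0091 instead of 0.025.
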